#### Pharmaceutical care plan

The purpose of the pharmaceutical care plan is to organize all of the pharmaceutical care agreed upon by the pharmacist, the GP, the practice nurse and the patient to achieve the goals of pharmacotherapy by addressing, resolving and preventing drug therapy problems. Together they formulate a care plan and the pharmacist specifically is responsible for the monitoring and the follow-up evaluation of the care plan and pharmacotherapy.

After establishing the drug therapy problems they are categorized based on a medical condition and on the drug therapy. When multiple drug therapy problems are present, they are prioritized based on the patient's perspective, focussing on those that causes the most concern and which one the patient is willing to address. The next step is to set the goals of the drug therapy and to agree on the interventions to achieve these goals. The interventions include start, stop or switch drug therapy, adjusting the dosage regimens or formulation, monitoring of drug therapy, referral to other clinician and individualized patient counselling and education. All these interventions are documented in the pharmaceutical care plan with detailed information on who is responsible for a certain action (GP, pharmacist or practice nurse), when the action will be taken and when it will be evaluated.

#### Monitoring and follow-up evaluation of care plan and pharmacotherapy

The focus of the monitoring and follow-up evaluation of pharmacotherapy is on the implementation of the pharmaceutical care plan. The pharmacist, the GP and if needed the patient, verify if all planned interventions are completed and they examine the outcomes of the documented drug therapy problems. They also assess if the goals of drug therapy are achieved. At this evaluation moment it is possible to plan new interventions to achieve previously documented goals of therapy or to solve previously identified drug therapy problems. The pharmacist documents the outcomes and possible new interventions in the care plan.

#### Control group

Patients in the control group receive usual care from their GP, pharmacist, practice nurse and other primary health care staff. This care consists of repeat prescriptions and medication surveillance according to the current clinical guidelines.

### Outcomes

The primary outcome of the study is the frequency of hospital admissions related to medication within the study period of 12 months of each patient. Two independent clinical pharmacists assess all admissions for a causal relationship between the reason for admission and the medication use, prior to the admission. This is done by reviewing the, blinded, discharge letter combined with the medical and medication data from an electronic Case Report Form (CRF), according to the adjusted Kramer algorithm[17].

The secondary outcomes are survival, quality of life, adverse drug events and severe adverse drug events. The quality of life is measured by the EuroQol EQ5D combined with the VAS (visual analogue scale) questionnaire at the start of the inclusion period and at the end of the inclusion period, after 12 months[18]. The pharmacist and the GP ask the patient at the end of the study period about symptoms of the past 3 months. They report and assess the adverse drug events according to the adjusted Kramer algorithm[17] combined with National Coordinating Council for Medication Error Reporting and Prevention (NCC MERP) scheme for categorisation of the severity of the events[19].

Other outcomes are the frequency and type of drug therapy problems (table 2) as documented in the pharmaceutical care plans over the intervention period. Two independent pharmacists code from the care plans, all the drug therapy problems, the proposed and executed intervention combined with the drug therapy. They meet to reach consensus when needed.

### Sample size

We expect to achieve an effect of 50% reduction of medication-related hospital admissions[2,20]. It seems possible to include 50 intervention patients from one intervention GP and 50 control patients from one control GP in one pharmacy practice, in a period of 12 months with a follow-up period of 12 months. To show a statistically significant difference between the intervention and the control arm with an expected prevalence of 0.01 (1%), we plan to include 14200 patients, 7100 in each arm, from at least 142 pharmacy practices and at least 284 GP practices to participate in the PHARM-study[21,22]. This is based on an alpha of 0.05 and a power (1-beta) of 0.8. It should be noted that the prevalence of HARM is expected to be higher in the group eligible for inclusion in the study.

#### Distribution of inclusion criteria

To determine the size of the population at risk and therefore eligible for inclusion, we searched the 'Kring-kubus-database'[23]. This database contains anonymous drug dispensing data from 100 (5.5%) community pharmacies, spread throughout the Netherlands, belonging to the franchise organization 'Kring-apotheek' (n = 330). In the Dutch community pharmacies, the drug history of individual patients can be considered as nearly complete because most patients visit only one single pharmacy[24]. This database includes drug-dispensing data from 719,022 patients with patient related information (age, sex, unique anonymous identifier), information on the dispensed drug (chemical substance coded according to the Anatomical Therapeutic Chemical (ATC) system[25] and dispensed product), date of dispensing, amount dispensed and prescribed dosage regimen. Patients who complied with the defined risk factors and therefore with the inclusion criteria as well (table 1), were selected from the database by using Microsoft Access. The use of the drug-dispensing data was performed in compliance with the Dutch privacy regulations.

We found that in an average pharmacy practice 6.4% (range: 1.5 - 15.0%) of the patients had a high risk of being admitted to hospital with a medication-related cause, according to the HARM-risk model. In an average Dutch pharmacy practice the size of this high-risk population was around 450 patients, enough eligible patients for participating in the PHARM-study. The type of drug (ATC class A; alimentary tract and metabolism or ATC class B; blood and blood forming organs) risk factor was the most common risk factor in the population of a pharmacy: 37.2% (range: 23.8 - 48.8%), while non-adherence was the smallest risk factor in the population of a pharmacy: 22.4% (range: 15.6 - 37.7%). The relative numbers of high risk patients per risk factor in the Dutch pharmacies and the distribution of these risk factors are presented in the box plots in figure 2. The numbers of high-risk patients per risk factor and the overlap between the risk factors are presented in the Venn diagram in figure 3.

**Figure 2 F2:**
[figure not shown]
**Proportion of the patients at HARM risk in a pharmacy with the distribution of the risk factors in the pharmacies in the 'Kring-kubus' database**.

**Figure 3 F3:**
[figure not shown]
**The number of high-risk patients per risk factor and the overlap between the risk factors (total patient population: 719,022)**.

### Randomisation

Cluster randomisation takes place after informed consent of the participating GPs and pharmacists on a GP level and before the selection of patients. For every pharmacist a random selection of the intervention GP is made. The other participating GP becomes the GP who will include control patients.

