## Methods/Design

### Participants

Only patients at high risk for a medication-related hospital admission are included in the study. To identify these patients we used risk factors from the HARM study as inclusion criteria[2]. This resulted in four criteria regarding age, polypharmacy, type of drug class used and non-adherence[14]. (See table 1 for detailed information on inclusion criteria) Patients could be included if they met all four of these criteria

**Table 1 T1:** Definition of the inclusion criteria of the PHARM-study

Criterion	Definition
65 years or older	65 Years of age or older, at the time of inclusion.

polypharmacy	Five or more drugs with different chemical substances. Every separate drug is prescribed and dispensed, at least 3 times in the 12 months before inclusion and dispensed at least once in the 6 months before inclusion.

ATC A or ATC B drug	One or more drugs from the Anatomical Therapeutic Chemical (ATC)[25] class A; "alimentary tract and metabolism" or ATC class B; "blood and blood forming organs". At least one of each drug prescribed and dispensed in the 12 months before inclusion.

non-adherence	At least one drug with a refill rate below 0.8 or above 1.2 This refill rate was calculated by dividing the number of dispensed daily doses, by the number of days between the first and the last prescription dispensed. The refill rate was calculated for all chronically prescribed drugs, as defined above under polypharmacy, of which at least 60 daily doses were dispensed in the 12 months before inclusion. The number of dispensed daily doses was calculated by summing the dispensed daily doses between the first to the last prescription date and multiplying it by factor 1.1 to correct for irregular drug use and early collection of the prescription. The refill rate was only calculated for oral and inhalation drugs with a clearly prescribed dose regimen. It was therefore not calculated for PRN (Pro Re Nata = as needed) drugs.

The number of included patients is limited to the capacity of the GP and the pharmacist. If too many patients are eligible for inclusion, random selection by computer based on patient serial number, is used within the eligible group of one GP and pharmacist, to comply with the limit. The pharmacist and GP both can include patients in 2008 and 2009, with a follow-up period of 12 months.

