Patients are excluded if they are resident in a nursing home, if their life expectancy is less than three months or if they will not give informed consent. Patients have to be withdrawn from the study when they are no longer a patient of the participating GP or pharmacist. This is possible when a patient moves to another area or to a nursing home or when a patient withdraws his/her informed consent.

The study is conducted in agreement with the principles of the Declaration of Helsinki (Edinburgh 2000) and was approved by the medical ethical review board of METOPP (Medisch-Ethische Toetsing Onderzoek Patiënten en Proefpersonen). The patient's pharmacist explains the procedure, possible benefit and burden of participation in the study to each patient and provides an informed consent form approved by METOPP. The patient is asked to sign the form prior to inclusion into the study. Patient data from this study are coded by the patient's own pharmacist. Analysing and publication of the results of this study will be performed anonymously.

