This study also has some limitations. First, selection bias may occur by just including patients who are willing to cooperate in the intervention. However, the same selection will take place in the control group because they also have to cooperate in completing the questionnaires. Second the selection of the participating pharmacist and GPs is based on voluntary participation. Only motivated couples of GPs and a pharmacist who established a good cooperation will participate in the study, which hampers the generalizability. But in case the intervention shows an effect, these participating GPs and pharmacists can be a role model for their colleagues in the region. A third limitation is the extensive and therefore demanding intervention. It is thinkable that it will not be implemented as described in the protocol because this is not possible or feasible in daily practice. A fourth limitation is the selection of intervention and control patients on a general practice level but from the same pharmacy which implies that control patients are cared for by the same pharmacist as the intervention patient. This possibly leads to contamination bias, but we do not expect that the pharmacist will provide other care than usual care to the control patients. A fifth limitation is the assessment of the ADEs which will be done by the patient's own pharmacist and GP who are not blinded to the assignment to intervention or control group. Knowing to which group the patient is assigned, may possibly affect their judgement of ADEs, which can potentially lead to the detection of more ADEs in the control group. On the other hand an advantage may be that they know their patients so they can make a better judgement if the symptoms are related to the medication or to a disease.

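### Patients are identified, excluded and consented after GP allocation is fixed, so the arms can differ in baseline risk, in either direction

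*Protocol article*

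**What the plan says.** Under Randomisation, the protocol article states: "Cluster randomisation takes place after informed consent of the participating GPs and pharmacists on a GP level and before the selection of patients." One GP per pharmacist is drawn at random for the intervention, and "The other participating GP becomes the GP who will include control patients."

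Under Participants, consent is the pharmacist's task: "The patient's pharmacist explains the procedure, possible benefit and burden of participation in the study to each patient and provides an informed consent form." It comes before entry: "The patient is asked to sign the form prior to inclusion into the study." The exclusions are nursing-home residence, a life expectancy under three months and refusal of consent. No assessor is named for them. Inclusion itself is open to both pharmacist and GP.

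A computer draw limits discretion in one situation: "If too many patients are eligible for inclusion, random selection by computer based on patient serial number, is used."

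The Discussion lists the shared pharmacist as a limitation, "which implies that control patients are cared for by the same pharmacist as the intervention patient." It also concedes selection by willingness to cooperate, but sets this aside because "the same selection will take place in the control group because they also have to cooperate in completing the questionnaires."

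**The concern.** In a cluster trial, randomising the cluster protects the patient-level comparison only if patients enter in the same way whatever arm their cluster is in. Here the arm is settled first, and the steps that decide who enters come afterwards. If those steps filter patients differently by arm, recruited patients can differ in underlying risk before any care is given.

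This would affect medication-related admissions, survival, quality of life and adverse drug events alike. It would be hard to repair once recruitment is done. Random effects for pharmacist and GP model correlation within clusters, not a systematic difference in who was recruited. The blinded review of discharge letters protects outcome assessment, not entry.

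**Working it through.** **Step 1: what remains open after allocation**

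| Entry step | Source | Open to differential selection? |
|---|---|---|
| Age, polypharmacy, drug class, refill rate | Participants, Table 1 | Little; rule-based on age and dispensing data |
| Computer draw | Participants | No, where used; it applies only when the eligible exceed capacity |
| Life expectancy under three months | Participants | Yes; a judgement, assessor not named |
| Individual consent | Participants | Yes; sought by the pharmacist who delivers the intervention |

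The draw may be common. Distribution of inclusion criteria gives about 450 high-risk patients in an average pharmacy, and Sample size needs 50 + 50 = 100. The share of the 450 belonging to the two participating GPs is not given. The draw works within the eligible group to meet a capacity limit and does not govern who consents.

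The article does not say outright that the pharmacist knows the allocation when seeking consent. This is inferred: each GP includes patients for one assigned arm, and the pharmacist carries out the intervention.

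**Step 2: is selection the same in both arms?** The Intervention section describes an anamnesis, a review, a care plan with possible therapy changes, and follow-up evaluation over several encounters. Control group describes usual care; the Discussion adds questionnaires. The burden differs, so a shared questionnaire does not make selection equal.

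**Step 3: can the analysis detect or correct it?** Data analysis examines age, gender, number of diseases, number of drugs and refill rate, which covers measured factors only. Cognitive impairment is named as a risk factor in Background, yet Table 5 marks cognition as recorded for intervention patients only, so balance on it cannot be checked.

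**Step 4: scale, under assumptions**

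Inputs from Sample size: 1% (read as the control risk), a 50% reduction, alpha 0.05 (taken as two-sided), power 0.8, 7,100 per arm, 50 per GP.

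Reproducing the planned size, unclustered:

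n = [1.96·√(2·0.0075·0.9925) + 0.8416·√(0.01·0.99 + 0.005·0.995)]² / 0.005² = 4,673 per arm.

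7,100 / 4,673 = 1.519, an intracluster correlation (ICC) of 0.519/49 = 0.0106. With continuity correction n = 5,065, giving 1.40 and an ICC of 0.0082. The article states no ICC, so the design effect is back-calculated.

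With no true effect, control events = 7,100 × 0.01 = 71 and intervention events = 71r, where r is an assumed baseline risk ratio:

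- SE = √[1.519 × (1/71 + 1/(71r))]
- shift = |ln r| / SE
- two-sided type I error = Φ(−1.96 + shift) + Φ(−1.96 − shift)

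| r | Intervention events | SE | Shift | Type I error |
|---|---|---|---|---|
| 0.9 | 63.9 | 0.213 | 0.496 | 7.9% |
| 0.8 | 56.8 | 0.219 | 1.017 | 17.4% |
| 0.7 | 49.7 | 0.228 | 1.565 | about 35% |

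A pooled two-proportion test gives 7.9%, 17.6% and 35.2%. With no clustering it gives 9.4%, 24.3% and 49.5%. At a 2% control risk with design effect 1.52 it gives 10.9%, 30.7% and 61.2%; Sample size itself expects a risk above 1% in eligible patients.

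In the other direction, suppose higher-risk patients enter the intervention arm (r = 1.1 or 1.2) and the true effect is a 50% reduction. Power then falls from 80% to 70% or 58%.

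**The case against.** The best defence is that little discretion is left. Eligibility comes from dispensing data, the draw may often choose the patients, baseline characteristics are analysed, and the authors acknowledge selection bias. This stands as far as it goes: it narrows the opening to the life-expectancy judgement and consent. It does not close it, and the acknowledgement concerns willingness to cooperate, not a recruiter who knows the arm.

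A reader might infer more than the article supports:

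- **That the pharmacist alone picks and excludes patients.** Inclusion is by pharmacist and GP, and nobody is named as applying the exclusions.
- **That controls are asked for questionnaires only.** Data analysis describes an interview feeding the CRF without restricting it by arm, and Outcomes has all patients asked about symptoms at the end. Follow-up evaluation involves the patient only where needed. The consent form is not shown. The burden is unequal, but the contrast is smaller than that reading suggests.
- **That allocation must be withheld until every patient has consented.** Sample size foresees 12 months to include the patients, and Support has training before the intervention period that the control GP does not receive. The intervention GP must be known before all consent can be complete.

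**Conclusion.** The concern holds as a design weakness that permits differential recruitment. The order of events is stated in the article, so this is not detail left to another document, and the Discussion's claim of identical selection does not hold.

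The article shows that the arms can differ in baseline risk, not that they will. Lower-risk patients in the intervention arm would manufacture an effect; higher-risk patients would hide one. The type I errors of about 7.9%, 17.4% and 35% rest on assumed baseline ratios of 0.9, 0.8 and 0.7, a 1% risk and a back-calculated design effect of 1.52. They show how sensitive the test is, not a predicted bias.

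**What to change.** 1. Amend Randomisation so that, for each pharmacist, the eligibility query, the computer draw and the exclusions are completed and locked for both GPs before the allocation is released. Name who applies the exclusions.
2. Invite patients from the locked list in list order, with one common invitation text for both arms.
3. Report eligible, excluded, invited and consented numbers per GP.
4. Replace the Discussion's same-selection sentence with an acknowledgement that consent after allocation can select differently by arm.

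The cost is revised wording, a controlled release of allocation and a short delay at each pharmacy before release. GP-level randomisation and sample size are unchanged. Consent would still follow allocation, so some risk remains; the counts in item 3 make differential uptake visible but do not remove it.

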### Data analysis

From each included patient data are collected in an electronic CRF containing: patient data, medical history and complaints, clinical data, quality of life and visual analogue scale, drug history with drug-allergies and drug-intolerabilities and a part with information on hospital admissions and adverse drug events. Detailed information on the data collected in the CRF can be found in table 5. The pharmacist and the GP complete the CRF with data from the pharmacy database, the GP database and from the interview with the patient. The collected data are based on literature and present guidelines[26-28].

**Table 5 T5:** Data collection; content of case report form (CRF)

Part	Data content
Patient data	• patient ID* • age*^§^ • gender*^§^ • pharmacist*^§^ • GP*^§^ • weight^#/+^ • lengths^#/+^ • diet^+^ • alcohol consumption^+^ • smoking habits^+^ • cognition^$^ • abilities/disabilities^+^ • daily activities^+^ • former education\language^+^ • religion^+^ • home situation^+^ • home help^+^ • carer^+^ • medication aids^+^ • other relevant information (free text) ^+^

Medical data	• acute medical conditions (menu, coded with ICPC-code[31])^#^ • chronic medical conditions (menu, coded with ICPC-code[31])* ^#^ • current complaints or symptoms (menu, coded with ICPC-code[31]) ^#^ • significant past medical conditions or procedures^#^ • other relevant health information (free text) ^#^

Clinical data	• laboratory values^#^ • blood pressure^#^ • temperature^#^ • weight^#^ • other relevant measured clinical data^#^ available clinical data is collected from 12 months before inclusion till the end of the inclusion period.^#^

Medication data	full drug history: all dispensed drugs from 12 months before inclusion till the end of the inclusion period^§^, containing information on: • chemical substance (menu, coded with ATC-code[25]) ^§^ • dispensed product (extracted from pharmacy database)* ^§^ • dispensed amount (extracted from pharmacy database)* ^§^ • dispensing date (extracted from pharmacy database)* ^§^ • prescribed dose (extracted from pharmacy database)* ^§^ • over the counter (OTC) drugs^§, +^ • vitamins, dietary or nutritional supplements^§, +^ • other health products^§, +^ • medical devices^§, +^ • drug allergies^§, +^ • intolerabilities or adverse drug events^§, +^

Study outcomes	• hospital admissions (discharge letter as appendix)^#^ • date of each admissions^#^ • reason for eacht admission^#^ • quality of life; EQ5D score (at t = 0* and t = 12 months)^+^ • visual analogue scale score(at t = 0* and t = 12 months) ^+^ • adverse drug events (ADE) with symptom, related drug and timing information (at t = 12 months) ^+, #^ • severity of the ADE^+, #^

Pharmaceutical care plan^$^	• DTPs (according to the Subjective-Objective-Assessment-Plan (SOAP) notes[29]) • therapy goals • priorities • interventions • clinician who is executing the action • date of action • date of evaluation of the action

* obligatory; ^$ ^for intervention patients only

^# ^Obtained from medical record

^§ ^Obtained from medication record

^+ ^Obtained from the patient during pharmaceutical anamnesis or questionnaire

For the intervention patients the CRF also contains a separate part for documenting the pharmacotherapy review, the pharmaceutical care plan and monitoring and follow up evaluation of pharmacotherapy. In this plan information is organised according to drug therapy related problems with the Subjective-Objective-Assessment-Plan (SOAP) notes method[29]. The assessment and evaluation of the different drug therapy problems are subsequently documented and prioritised and the subsequent interventions are documented with specific information on who of the clinicians is taking the action, when the action is taken and when the action is evaluated.

Data from the digital Excel CRF and from a Microsoft Access database are combined and further analysed by using R, version 2.6.2. In R mixed-effects Cox models[22] are designed to study the effect of the intervention on hospital admissions related to medication and the effect on survival, quality of life and adverse drug events. All available patient data are included. The pharmacist and the GP are integrated as random effects in the models. P-values < 0.05 are regarded as statistically significant. The two-sided 95% bootstrap percentile confidence intervals are computed using 1000 replications. Bootstrap samples are obtained by random sampling GP's or patients with replacement from the population. To assess the model's goodness of fit we create plots of outcome versus follow-up time, versus number of diseases and examined residuals. The influence of the baseline characteristics such as age, gender, number of physicians, number of diseases, number of drug prescribed, refill rate and follow-up time are also analysed using linear mixed-effects models or generalized linear mixed-effects models.

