**Methods/Design:**

The PHARM-study is designed as a cluster randomised, controlled, multi-centre study in an integrated primary care setting. Patients with a high risk of a medication related hospital admission are included in the study with randomisation at GP (general practitioner) level. We aim to include 14200 patients, 7100 in each arm, from at least 142 pharmacy practices.

The intervention consists of a patient-centred, structured, pharmaceutical care process. This process consists of several steps, is continuous and occurrs over multiple encounters of patients and clinicians. The steps of this pharmaceutical care process are a pharmaceutical anamnesis, a review of the patient's pharmacotherapy, the formulation and execution of a pharmaceutical care plan combined with the monitoring and follow up evaluation of the care plan and pharmacotherapy. The patient's own pharmacist and GP carry out the intervention. The control group receives usual care.

The primary outcome of the study is the frequency of hospital admissions related to medication within the study period of 12 months of each patient. The secondary outcomes are survival, quality of life, adverse drug events and severe adverse drug events. The outcomes will be analysed by using mixed-effects Cox models.

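### Cox models are prescribed for quality of life, a score at two fixed times with no event, and for adverse drug events over a follow-up that their 3-month recall window does not match

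*Protocol article*

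**What the plan says.** In the Data analysis section the article states: "In R mixed-effects Cox models[22] are designed to study the effect of the intervention on hospital admissions related to medication". The same sentence continues: "and the effect on survival, quality of life and adverse drug events". The abstract (Methods/Design) is broader and makes no exception: "The outcomes will be analysed by using mixed-effects Cox models".

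The Outcomes section says that the EQ5D and VAS are taken "at the start of the inclusion period and at the end of the inclusion period, after 12 months". Table 5 agrees: "quality of life; EQ5D score (at t = 0* and t = 12 months", where the asterisk marks the t = 0 item as obligatory. The VAS row has the same two times.

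For adverse drug events the Outcomes section says: "The pharmacist and the GP ask the patient at the end of the study period about symptoms of the past 3 months". Table 5 adds that these events are recorded at month 12 with the symptom, the related drug and timing information, and marks the source as both the patient and the medical record.

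The Data analysis section also names linear and generalized linear mixed models. The sentence that names them is about the influence of baseline characteristics such as age, number of diseases and refill rate.

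**The concern.** A Cox model compares the rate at which events occur over time, so it needs an event, an event time and a period at risk. Quality of life here has none of these: it is a score observed at two scheduled points. No derived event, such as time to a stated deterioration, is defined. Adverse drug events do have occurrences and some timing, but they are sought by one backward-looking interview, and no time origin or risk period is tied to that window.

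At stake is whether two of the effects in the study's objective have a prespecified analysis that can be carried out. Quality of life does not. Its model would have to be chosen later, in a trial where the treating pharmacist and GP know the allocation. For adverse drug events, an analyst who followed the text literally could treat months outside the interview's reach as observed and event-free.

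**Working it through.** The article gives no figure for either outcome, so the check compares model with data and then works out what a Cox fit would return.

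**Data against model**

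| Outcome | How it is observed | Event time | Model for the intervention effect |
|---|---|---|---|
| Medication-related admissions | Date of each admission (Table 5) | Yes | Cox |
| Survival | Time to death | Yes | Cox |
| EQ5D and VAS | Score at t = 0 and t = 12 months | None defined | Cox |
| Adverse drug events | End-of-study interview on the past 3 months; timing recorded | Within the recall window | Cox |

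**Quality of life.** Suppose each month-12 assessment is entered as the event, with everyone at the same time. Let n1 and n0 be the arm sizes, n = n1 + n0, and b the log hazard ratio. With Breslow ties the score equation is

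n1 = n × n1·e^b / (n0 + n1·e^b).

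This gives n0 + n1·e^b = n·e^b, hence e^b = 1 and b = 0. The EQ5D and VAS values appear nowhere in the equation. A numerical check used 2000 simulated patients with assumed mean scores of 0.70 and 0.73 (SD 0.2). It returned a log hazard ratio of exactly 0 with standard error 0.0447, which is sqrt(1/1000 + 1/1000). If actual visit dates were used instead of a common time, the model would compare when patients were assessed, still not how they scored.

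**Adverse drug events, yes or no, all placed at month 12.** Let d1 and d0 be the numbers of patients with an event. The score equation is

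d1 = (d1 + d0) × n1·e^b / (n0 + n1·e^b),

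which solves to e^b = (d1/n1) / (d0/n0), the risk ratio. In simulation with assumed risks of 30% and 15%, exp(b) was 0.466 and the observed risk ratio was 0.466. So even without event times a Cox fit gives an interpretable point estimate here.

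**Window against follow-up.** The interview covers 3 of 12 months, that is 3/12 = 25% of follow-up. It does not ask about the other 12 − 3 = 9 months. A patient who dies or leaves before month 12 has no such interview. Table 5 also lists the medical record as a source, so some earlier events might be picked up, but the article gives no rule that makes the first 9 months a period of complete ascertainment.

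These checks used a fixed-effect Cox model. Adding pharmacist and GP random effects does not supply an event time or bring the score into the model.

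**The case against.** The best defence is that the sentence is compressed drafting. The section does name linear mixed models; these need a continuous outcome, and EQ5D and VAS are the evident ones. The authors may well have meant them for quality of life. That is plausible, but the text attaches those models to a different question, and the abstract sentence points the same way as the error. The intended reading should be written down.

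For adverse drug events the defence has more force. A reader might infer that no event times exist and that the effect cannot be validly estimated. The documents do not support this: Table 5 records timing information, and the calculation above shows that a tied Cox fit returns the risk ratio. What remains is the mismatch between the recall window and the 12-month follow-up.

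A reader might also infer an error in the primary analysis, because the Outcomes section says "The primary outcome of the study is the frequency of hospital admissions related to medication within the study period" while the model is Cox. The documents do not support that either. The date of each admission is collected, a Cox model is legitimate for such data, and whether first or all admissions enter it can be left to a full analysis plan.

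Nor does the article say that the obligatory t = 0 score would be discarded; it says that all available patient data are included. Finally, quality of life is secondary, and the sample size concerns admissions only. That limits the consequence but does not make the stated analysis workable.

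**Conclusion.** The point stands for quality of life. As written, the article prescribes a model that cannot estimate the intervention effect on EQ5D or VAS, and no other model is assigned to it. The result b = 0 assumes that the month-12 assessment is taken as the event at a common time; the article defines no other event.

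For adverse drug events the conclusion is limited. A Cox model over 12 months does not match an interview that covers the last 3, and the risk period is undefined. The estimate is not thereby shown to be invalid.

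The loss of precision or the bias cannot be sized from the documents, because they give no quality-of-life variances or correlations and no adverse drug event rate. Survival, the primary outcome and the sample size are untouched.

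**What to change.** - **Quality of life:** analyse the month-12 EQ5D score and the month-12 VAS score each with a linear mixed model, with the corresponding t = 0 score as covariate and pharmacist and GP as random effects.
- **Adverse drug events and severe adverse drug events:** use a mixed-effects logistic model for any event, or a mixed count model for the number of events, in the 3-month window, with the same random effects. Alternatively keep Cox, but state the time origin and restrict the risk period to that window.
- **Data analysis section and abstract:** limit the Cox statement to medication-related admissions and survival (and to adverse drug events only if the restricted risk period is adopted), and name the other models.

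The cost is a few sentences of analysis text. The scores at both times, the event data and the pharmacist and GP identifiers are already on the case report form, so no new data are needed and the sample size does not change. The wording should be settled before outcome data are compared by arm.
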